### 3.4. Data collection and management

All data will be pseudonymized. Unique IDs will be kept in a password-protected, encrypted network accessible only to the PI and study staff. Device fitting and troubleshooting will be documented, and adverse events will be immediately reported to the study team and logged in the participant manual. In our feasibility study, it is more crucial to ‘understand the reasons’ contributing to missing data rather than ‘deal with’ them. We will therefore describe the missing data and explore the mechanism in the semi-structured interview.

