#### 2.3.2. Measurements for the primary objectives.

**Taiwanese Version of the Quebec User Evaluation of Satisfaction with Assistive Technology (T-QUEST) [30**]: The T-QUEST will assesses satisfaction with wearables and related services. There are 13 items scored from 1 (very dissatisfied) to 5 (very satisfied), and will be administered to both sides of the dyads at Day 42 (for Re-Timer) and Day 56 (for Geneactiv). If the patient cannot complete the questionnaire, only the caregiver will respond.**Participant Manual:** Each participant will be provided with a personalized manual. The cover will include their name, the study started date, and a QR code for immediate contact with the research team. The manual contains a plain-language introduction to the study’s objectives and tables for participants to record the daily timing and duration of Re-Timer usage and qualitative feedback regarding wearing experience. These subjective records are essential for validating the feasibility of light interventions among dementia patients and their caregivers in rural Taiwan.**Actigraphy Data:** Utilizing the GGIR (an R-based automated package), compliance will be assessed through raw data extracted from the Geneactiv devices. This analysis allows us to calculate precise Geneactiv wearing duration and percentage (Time worn/Total study duration) across the 8-week study period. By examining the distribution of wear time, we can evaluate the long-term acceptability of research-grade wearables in dementia patients and their caregivers in rural Taiwan. These metrics will serve as a primary indicator of whether the protocol is practical for real-world application.**Semi-Structured Interviews:** The interviews will extend from T-QUEST topics to explore participants’ and caregivers’ experiences with both devices, including acceptability, ease of use, comfort, and challenges. Open questions will first be used, followed by iterative, in-depth probing that focuses on convenience, regularity, motivation, and satisfaction. Through this back‑and‑forth process, participants will be encouraged to provide everyday-life examples so that they can fully articulate their experiences and feelings when using the devices. Each interview will last approximately 30–60 minutes in a setting comfortable for participants and caregivers to ensure natural and reliable data collection. Audio recordings will be transcribed and analyzed using thematic analysis to explore perceptions of wearable devices for assessing and managing neuropsychiatric symptoms after trial participation. See supporting information for the interview guide.

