**Fig 2 pone.0342136.g002:**
[figure not shown]
The two study devices. Left: Geneactiv research-grade actigraphy; right: Re-Timer circadian regulator. (Image taken by the authors.).

**Re-Timer circadian regulator**: Re-Timer is an eyewear emitting 500-nm blue-green visible light with no ultraviolet hazard (Fig 2, right). The device power/irradiance: 506 lux, 230 μW/cm². Theoretically, the light emitted could reduce melatonin secretion and enhance alertness. Prior studies support applicability and safety in adults, those with certain psychiatric conditions, and older adults.

**Device-wearing and assessment schedule** Participants will be retained in the study for 12 weeks (as in Fig 3), during which they will be advised to continue their usual daily routine/care, and will be advised to wear the device for up to 8 weeks, based on the following schedule. On Day 1, baseline demographics and initial assessments (PSQI, NPI-Q, and CBI) will be collected, and the Geneactiv monitoring will start. This is followed by Day 15, where PSQI and NPI-Q are repeated and the Re-Timer intervention begins (daily 30–60 min). On Day 42, assessments including PSQI, NPI-Q, CBI, and a T-QUEST-based semi-structured interview for Re-Timer will be conducted as the blue-green light intervention concludes. Subsequently, on Day 56, PSQI, NPI-Q, and a T-QUEST-based semi-structure interview for Geneactiv will be completed, marking the end of the Geneactiv monitoring period. Finally, a follow-up assessment of PSQI, NPI-Q, and CBI will be performed on Day 84.

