**Fig 3 pone.0342136.g003:**
[figure not shown]
Study flow diagram. The study lasts for 12 weeks. Participants will be advised to wear the Geneactiv wrist actigraphy for up to 8 weeks, and the Re‑Timer circadian regulator for up to 4 weeks. They will complete five rounds of assessments on Day 1 (baseline before any device-wearing), Day 15 (baseline before Re-Timer), Day 42 (immediate post-Re-Timer), Day 56 (post-Re-Timer and Geneactiv), and Day 84 (trial completion).

More specifically on the device-wearing:

**Geneactiv**: Days 1–56 (8 weeks) continuous wear. The device is waterproof, but participants may remove the device anytime during the trial if discomfort occurs.**Re-Timer**: Days 15–42 (4 weeks) ≥30 min each time, and up to 60 min/day. The participants will be recommended to wear it twice a day, one in the morning, one in early afternoon, but can remove the device and stop to use at anytime if discomfort occurs. Day-care/hub participants may choose on-site staff-assisted wear and/or home wear. Correct positioning will be taught by the study team members. A participant manual will be provided to record the device-wearing time windows each day and any feedback.

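### Interviews and T-QUEST are fixed at Days 42 and 56, so early study withdrawals get neither and no interview can explain data missed at Day 84

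*Protocol article*

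**What the plan says.** Section 3.4 of the protocol article sets the priority: "it is more crucial to ‘understand the reasons’ contributing to missing data rather than ‘deal with’ them". It then names the route: "We will therefore describe the missing data and explore the mechanism in the semi-structured interview". No other route is named there.

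Section 2.4 dates the interviews. For Re-Timer: "On Day 42, assessments including PSQI, NPI-Q, CBI, and a T-QUEST-based semi-structured interview for Re-Timer will be conducted". For Geneactiv: "on Day 56, PSQI, NPI-Q, and a T-QUEST-based semi-structure interview for Geneactiv will be completed". The last contact has no interview: "a follow-up assessment of PSQI, NPI-Q, and CBI will be performed on Day 84".

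T-QUEST follows the same calendar. Section 2.3.2 says it "will be administered to both sides of the dyads at Day 42 (for Re-Timer) and Day 56 (for Geneactiv"), and section 3.1 repeats the two days. Section 3.1 lists wear compliance, T-QUEST satisfaction and qualitative acceptability as the primary endpoints. Section 3.3 says the sample size rests mainly on assessing recruitment and retention. The article describes no interview, T-QUEST or other contact triggered by withdrawal.

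**The concern.** The plan sets aside statistical handling of missing data in favour of learning why data are missing. That is a reasonable choice for a feasibility study of 10 dyads, but it depends on the chosen tool reaching the people whose data are missing. An interview tied to a calendar day reaches only those still in the study on that day.

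Two things are at stake. First, the account of missing data would lack interviews with those who withdrew, although retention is a stated basis of the sample size and their reasons are among the main results. Second, two of the three primary endpoints would describe only those who remained. If people who leave tend to be less satisfied, the reported satisfaction is too favourable, and a later trial would be planned on it.

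**Working it through.** **Who is reached, from the schedule in sections 2.3.2 and 2.4**

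| Event | Re-Timer interview and T-QUEST (Day 42) | Geneactiv interview and T-QUEST (Day 56) |
|---|---|---|
| Withdraws from the study before Day 42 | not scheduled | not scheduled |
| Withdraws between Day 42 and Day 56 | obtained | not scheduled |
| Stops a device, stays in the study | obtained | obtained |
| Misses Day 84 only | obtained, but before the gap arises | obtained, but before the gap arises |

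**Sample size.** 10 dyads × 2 = 20 participants, as section 3.3 states. There is no power calculation to reproduce, and no dropout rate is given.

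**Share of questionnaires at Day 84.** Inputs are the schedules in section 2.3.3, counting one NPI-Q and one CBI per dyad.
- PSQI: 20 people × 5 = 100, of which 20 at Day 84.
- NPI-Q: 10 dyads × 5 = 50, of which 10 at Day 84.
- CBI: 10 caregivers × 3 = 30, of which 10 at Day 84.
- Total: 100 + 50 + 30 = 180, with 20 + 10 + 10 = 40 at Day 84. 40/180 = 22%.
- The last interview comes 84 − 56 = 28 days earlier.

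**Chance that the gap matters at all.** Assume each dyad independently has probability d of leaving before its interview. P(at least one of 10 lost) = 1 − (1 − d)^10.
- d = 0.1: 65%
- d = 0.2: 89%
- d = 0.3: 97%

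**Possible shift in mean T-QUEST item score (scale 1 to 5).** Assume completers average 4.0 and leavers would have averaged 2.5. Mean for all enrolled = 4.0(1 − d) + 2.5d.
- d = 0.1: 3.60 + 0.25 = 3.85
- d = 0.2: 3.20 + 0.50 = 3.70
- d = 0.3: 2.80 + 0.75 = 3.55

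Completers-only reporting shows 4.0 in each case.

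**Bounds without assuming how leavers feel.** For one group of 10 with responders at an assumed 4.0, give each missing person the lowest score (1) and then the highest (5).
- 1 missing: 0.9 × 4 + 0.1 × 1 = 3.7, to 0.9 × 4 + 0.1 × 5 = 4.1
- 2 missing: 0.8 × 4 + 0.2 × 1 = 3.4, to 0.8 × 4 + 0.2 × 5 = 4.2
- 3 missing: 0.7 × 4 + 0.3 × 1 = 3.1, to 0.7 × 4 + 0.3 × 5 = 4.3

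The bounds run both ways. The downward direction comes from the assumption that leavers are less satisfied. The bounds are wider downwards only because 4.0 is nearer the top of the scale.

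**The case against.** The strongest objection is that stopping a device is not leaving the study. Section 2.4 says a Re-Timer user "can remove the device and stop to use at anytime if discomfort occurs", and also that participants are kept in the study for 12 weeks. Someone who gives up Re-Timer on Day 20 and stays is still due both interviews and both T-QUESTs. A reader might infer that everyone who stops early goes unheard. The article does not support that, and this part of the objection stands in full.

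A reader might also infer that the interview is the only source, so that reasons are never learned for those who leave. That is too strong as well. The article provides a daily manual with wear times and feedback (sections 2.3.2 and 2.4), fitting and troubleshooting notes and an adverse event log (sections 3.4 and 3.5), and an outcome-sharing event after the study (section 3.6). These may yield some reasons. However, the text links none of them to missing data, and the manual's tables concern Re-Timer use and the wearing experience, not missed questionnaires or withdrawal.

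Third, this is a condensed article. A withdrawal form or exit contact may exist in the full protocol, the interview guide is in supporting information that is not shown, and section 2.3.2 contains a phrase about perceptions after trial participation that leaves interview timing a little open. If an exit contact exists, citing it would settle much of the point. What remains is that the article itself states a route and a fixed calendar, and the two do not fit its stated aim.

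Fourth, the effect on the overall conclusion is limited. Wear compliance is also a primary endpoint, and Geneactiv wear is expressed as time worn over total study duration, so early leaving should lower it. The Day 84 questionnaires are secondary and exploratory. Both are fair limits on the size of the concern.

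**Conclusion.** The point holds for two groups: participants who withdraw from the study before Day 42 or Day 56, and anyone with data missing at Day 84. For them the named route to the reasons is not available under the schedule as written. T-QUEST and the interviews would describe only those still in the study.

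The size cannot be taken from the document, which gives no dropout rate and no expected score. On the assumed values the overstatement of the mean item score is 0.15 to 0.45 points (4.0 against 3.85 to 3.55). The direction rests wholly on leavers being less satisfied, which is plausible but not documented. Nor is 20 an assured denominator: the plan compares patients with caregivers, for two devices on two days, and only the caregiver answers when the patient cannot.

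This is a cheap improvement to the design, not an error that invalidates it.

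**What to change.** 1. At study withdrawal, offer T-QUEST for each device the participant has actually used, with a brief exit interview from the existing guide, by phone if needed. Someone leaving before Day 15 has not used Re-Timer and would be asked only about Geneactiv.
2. Record the reason at every withdrawal and every missed visit. For Day 84 this needs a call to those who miss it, because a question asked at the visit cannot reach them.
3. In section 3.4, state that the manual, troubleshooting notes and adverse event log will also be used to describe reasons for missing data.
4. Report T-QUEST by device and by group with the number enrolled and the number responding, and show the result including early leavers beside the completers-only result.

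With 20 participants the cost is a few calls, using existing staff and the existing guide. The downside is that some scores will refer to shorter exposure, so the duration of use should be shown with them. Enrolment is expected to run to May 2026 (section 3.7). The change is best made early, since reasons not asked for at the time may be hard to recover.

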### 3.5. Safety monitoring

Participants may pause or stop device wear with any discomfort. Adverse events recorded with symptom descriptions and actions taken; referral pathways activated as needed. Serious adverse events (SAE) (e.g., hospitalization, ED visit, death) reported promptly and monitored; if three consecutive SAEs occur, the study will be temporarily halted.

### 3.6. Public and Patient Involvement (PPIE)

This study incorporates a robust Patient and Public Involvement and Engagement (PPIE) framework to ensure the current research and future studies are transparent, inclusive, and grounded in lived experience. An Advisory Group will be established, comprising study participants (patients and caregivers), trial-related clinicians, and experienced researchers. This multidisciplinary group will provide iterative consultation for study design: reviewing participant-facing materials for cultural and practical appropriateness during the design phase, addressing real-world implementation challenges, and assisting in the interpretation of feasibility metrics and qualitative findings.

In the post-study phase, the team will organize a dedicated outcome-sharing event to gather all participants and stakeholders. This event serves as a platform for knowledge translation, allowing the research team to present findings directly to the community while gathering final feedback on the protocol’s ecological validity. By involving stakeholders as active partners rather than passive subjects, this approach ensures the study design remains participant-centered and provides a refined foundation for future large-scale clinical trials.

### 3.7. Study timeline

The project has enrolled its first participant on November 18^th^ 2025, and enrollment is expected to be completed in May 2026. Recruitment will continue until the last participating dyad has been confirmed, and data collection is plan to be done before July 2026. The final results are expected to be presented in December 2026.

## 4. Expected outcomes and discussion

Based on the research objectives, this study anticipates the following three merits:

Improving the application of wearable devices for patients with BPSD: By evaluating the acceptability and feasibility of Geneactiv and Re-Timer devices, this study will provide an abundance of information to help optimize their design and usage, thereby increasing the willingness of patients with dementia and their caregivers to use these devices regularly in daily life.Collection of preliminary data on clinical efficacy: The study will generate initial data on the effects of Re-Timer on BPSD and sleep problems of AD patients and the stress and sleep on their caregivers. These findings will help assess whether the device can improve the quality of life for patients and caregivers and provide direction and baseline information for future large-scale studies.Exploring the impact of light and circadian rhythm on BPSD: By analyzing long-term activity patterns and light exposure data collected via Geneactiv, this study will explore the relationship between light, circadian rhythm, and changes in BPSD symptoms. This may offer clinically meaningful insights for developing new non-pharmacological interventions and improving the assessment and management of BPSD.

Overall, despite its smaller sample size, this pilot study will be the first dyadic study exploring the feasibility of applying two wearable devices concomitantly on AD patients with pre-defined BPSD and their caregiver. Under the context of global ageing, the burden of dementia has not only led to huge caregiver burden, but also heightened societal and healthcare costs. If proved feasible in rural Taiwan where both digital and health literacy and resources are limited, our study may be able to guide future research in designing more customized wearable-based dementia care models that ameliorate BPSD and reduce caregiver burden.

### 4.1. Trial registration

The trial has been pre-registered in ClinicalTrials.gov with identifying number: NCT07249918 (URL: https://clinicaltrials.gov/study/NCT07249918)
